Undertaking an RCT to evaluate the effects of a CEI on psychosocial outcomes is, however, challenging and a number of uncertainties need to be clarified before proceeding to a full-scale phase III trial. Firstly, the feasibility of undertaking a trial of a non-traditional intervention in a rehabilitation setting needs to be established. Art is an intervention in which preference for participation may strongly influence participant recruitment and attrition and therefore, before proceeding to a full trial, it is vital to identify the role of preference in recruitment and trial participation. Secondly, components of the intervention and their mechanisms of action need to be made explicit. Thirdly, the precise outcomes likely to be influenced by the intervention and corresponding appropriate measures that can be completed by stroke survivors need to be identified.

Selection of appropriate outcome measures is a particular challenge to researchers designing studies to measure the intervention effects of CEI. This is challenging given that the exact mechanisms by which art may influence psychosocial outcomes have not been fully established for stroke survivors. The present trial design is derived from an initial qualitative study that aimed to identify for the purposes of the trial, the components, mechanisms of action and perceived effects of an existing visual art CEI for stroke survivors receiving in-patient rehabilitation. Findings from the qualitative phase were used to design the feasibility trial intervention protocol and identify the outcomes to be evaluated to test the effects of the intervention. The purpose of the present study is to test trial processes to identify feasibility issues in running a CEI, to identify the primary outcome measure and to provide an assessment of effect size for power calculations for a full-scale Phase III trial. The purpose of this manuscript is to describe the trial design and protocol for a feasibility trial.

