### Sample size calculation

This is a feasibility trial therefore we have not undertaken a formal sample size calculation. A sample size of 40 participants in each group will be adequate to provide estimates of direction and magnitude of any effects, and to provide an estimation of variability for later sample size calculation. Previous literature shows that a sample size of between 30 and 36 per arm is adequate for a feasibility trial [55]. We based our sample size on that information, on our knowledge of likely participants to the art program, and on information from our previous experience of likely drop-out rates from stroke rehabilitation trials.

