To examine the effects of the intervention, a repeated measures analysis using mixed models will be conducted for outcomes, although these will not involve definitive hypotheses testing. Adjustment for baseline factors and mediating variables will be undertaken by adding these as covariates to give an idea of which factors are important in determining outcome. This will indicate where the intervention effects are likely to occur and will generate power calculations for a future definitive RCT. The measure with greatest difference as well as most relevance in the feasibility study will be selected as primary outcome measure, whilst taking into account proportions of missing data. Missing data will be examined for randomness, and if appropriate, multiple imputations will be conducted to replace missing values. Intention-to-treat analysis based on outcome evaluation of cases as randomized will be conducted to examine any important differences in findings. Reporting of results will adhere to Consolidated Standards of Reporting Trials criteria for the reporting of randomized controlled trials [57].

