To our knowledge, this is the first study aimed at examining the feasibility of using trial methods to evaluate the effectiveness of an art intervention for stroke survivors in rehabilitation. We hypothesize that participation in a CEI will improve the psychosocial outcomes for stroke survivors during and after rehabilitation. If shown to provide effect sizes, indicative of meaningful effects this intervention has the potential to address aspects of stroke recovery previously not addressed in rehabilitation, and will provide convincing evidence of benefits to healthcare providers and funders.

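### The pilot's observed differences help choose the definitive trial's primary outcome and also feed its power calculation, so the effect carried forward is biased upwards

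*Protocol article*

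**What the plan says.** Under Statistical analysis, the protocol article sets the rule for the definitive trial's endpoint: "The measure with greatest difference as well as most relevance in the feasibility study will be selected as primary outcome measure". A closing clause in the same sentence adds that completeness of the data will be weighed too. The sentence just before it says that the same modelling will produce the power calculations for that trial.

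Two earlier sections agree. The Background gives as one purpose of the study "to provide an assessment of effect size for power calculations for a full-scale Phase III trial". The Study aims section says that estimated effect sizes will inform both the choice of primary outcome and the sample size.

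On size, the Sample size calculation section says "This is a feasibility trial therefore we have not undertaken a formal sample size calculation" and "A sample size of 40 participants in each group will be adequate to provide estimates of direction and magnitude of any effects". It cites earlier literature ("Previous literature shows that a sample size of between 30 and 36 per arm is adequate for a feasibility trial") and relies partly "on information from our previous experience of likely drop-out rates from stroke rehabilitation trials", without giving a rate.

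The Outcome measures section names the Stroke Impact Scale as the likely primary outcome but leaves the final selection to this trial's findings. Neither shrinkage, nor a confidence-limit rule, nor a minimally important difference is stated as a safeguard on the effect carried forward.

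**The concern.** Each observed difference is a true effect plus sampling error. Favouring the measure with the largest difference favours the measure whose error happened to be positive and large, so its estimate is too high on average. If that estimate then sizes the next trial, the error passes straight into the sample size, which varies with one over the effect squared. The definitive trial could then be well short of its nominal power, on an endpoint chosen partly by chance.

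This concerns a rule the article states. It is not a detail that a separate analysis plan would be expected to supply.

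**Working it through.** **The plan's own figure.** No alpha, power, effect, SD or dropout rate stands behind 40 per arm, so it cannot be reproduced as a power calculation. It is consistent with the cited 30 to 36 per arm plus an allowance for dropout: 36/(1 − 0.10) = 40 and 30/(1 − 0.25) = 40. The 10% and 25% are assumptions.

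**Inputs.**
- From the article: n = 40 per arm, and seven instruments under Measures and measurement instruments.
- Assumed: true standardised effect d = 0.2 on every measure; correlation ρ between estimates of 0.3 to 0.5; two-sided alpha 5%; nominal power 90% (80% where stated); baseline correlation r of 0.5 to 0.7 for the adjusted case.

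**Step 1: precision of one difference.**
- Unadjusted: SE = √(2/40) = 0.224 SD; 95% half-width = 1.96 × 0.224 = 0.44 SD.
- Baseline-adjusted: SE = √[(2/40)(1 − r²)]. For r = 0.5 this is 0.194 (half-width 0.38); for r = 0.7 it is 0.160 (half-width 0.31).
- Chance of the wrong sign, Φ(−d/SE), unadjusted: 33% at d = 0.1, 19% at 0.2, 9% at 0.3 and 1.3% at 0.5. Adjusted, at d = 0.2: about 15% (r = 0.5) to 10% (r = 0.7).

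**Step 2: effect of selecting on size.** For K equally correlated estimates with the same true effect, the mean of the largest is d + SE × √(1 − ρ) × E(K), where E(K) is the expected maximum of K independent standard normals: E(3) = 0.846, E(7) = 1.352.

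| Candidates | ρ | Mean selected value, true d = 0 | Mean selected value, true d = 0.2 |
|---|---|---|---|
| 3 | 0.5 | 0.13 | 0.33 |
| 3 | 0.3 | 0.16 | 0.36 |
| 7 | 0.5 | 0.21 | 0.41 |
| 7 | 0.3 | 0.25 | 0.45 |

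Example: 0.2 + 0.2236 × √0.7 × 1.352 = 0.45. Simulation gives the same values. Three candidates corresponds to the Stroke Impact Scale, affect and self-esteem, which the Outcome measures section sets apart from the measures of underlying constructs. Baseline adjustment would multiply the excess over the true value by √(1 − r²), that is 0.87 to 0.71, if the correlations between estimates were unchanged.

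**Step 3: size the next trial on the selected value.** n per arm = 2(1.96 + 1.2816)²/d², rounded up; true power = Φ(0.2 × √(n/2) − 1.96).

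| Value used | n per arm | True power at d = 0.2 |
|---|---|---|
| 0.33 | 193 | 50% |
| 0.36 | 163 | 44% |
| 0.41 | 126 | 35% |
| 0.45 | 104 | 30% |
| 0.20 (correct) | 526 | 90% |

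**Step 4: remove the selection.** With the outcome fixed in advance, the pilot estimate is unbiased. Sizing on it is still unreliable: in 100,000 simulated pilots of 40 per arm, leaving out those with an observed effect of 0.1 SD or less, a trial sized for a nominal 80% had median true power of about 48% at d = 0.2 and 67% at d = 0.3.

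**Step 5: what the pilot can supply.** With 78 degrees of freedom, the 95% interval for the SD runs from about 0.86 to 1.19 times the estimate, which is usable for planning.

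**The case against.** The strongest reply is that size of difference does not decide alone. Relevance stands beside it in the same sentence, missing data are weighed, and the Outcome measures section adds completion, ease of use, variability and comparison between measures. The Stroke Impact Scale is already the provisional choice. This stands: a free maximum over seven interchangeable measures is an upper case, and the three-candidate figures are nearer to how the rule might work. The bias becomes smaller but does not vanish while the observed difference remains a criterion.

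It is also fair that √(2/n) ignores the planned baseline-adjusted mixed model, which would narrow the interval, and that the analysis disclaims definitive hypothesis testing. The definitive trial would have its own protocol.

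Some stronger inferences are not supported:
- A reader might infer that the article claims 40 per arm will establish direction and magnitude. It promises estimates of them, and an imprecise estimate is still an estimate. At a true effect of 0.5 SD the sign would rarely be wrong.
- A reader might see the Discussion phrase "will provide convincing evidence of benefits to healthcare providers and funders" as contradicting the disclaimer on hypothesis testing. That sentence is conditional on effect sizes that indicate meaningful effects. It is optimistic, but it is not an analysis rule.
- A reader might suppose that raw differences on 0–100 and 10–50 scales would be ranked against each other. The article speaks of effect sizes and nowhere specifies raw ranking.
- A reader might take effect estimation to be the study's main product. The Study aims section lists it last, after recruitment, preference, retention and acceptability.

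**Conclusion.** The concern holds in a limited form. The article makes observed difference one of several criteria for the definitive primary outcome and uses the same pilot effects for power, with no stated safeguard. On average this overstates the effect. For a true effect of 0.2 SD, the selected value would average 0.33 to 0.36 SD with three candidates and 0.41 to 0.45 SD with seven, and the resulting trial would have true power of about 44–50% or 30–35% against a nominal 90%.

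These figures assume equal true effects, correlations of 0.3 to 0.5, unadjusted estimates, and that size decides among the candidates. The inflation is an expectation, not a certainty in any one trial.

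Forty per arm is not itself at fault: the argument leaves its use for recruitment, retention and SD estimation untouched. The point should be fixed, but it does not threaten the validity of this feasibility trial.

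**What to change.** - **Statistical analysis:** delete greatest difference as a selection criterion. Choose the primary outcome on relevance, completion or missing data, and measurement properties.
- **Statistical analysis, Background and Study aims:** say that the SD and retention will come from this trial and that the definitive trial will be powered on an independently justified minimally important difference. Report pilot effects with confidence intervals, as a plausibility check only.
- **Sample size calculation:** add that the estimates of direction and magnitude will be imprecise. If ±0.44 SD is quoted, label it as unadjusted.

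The cost is wording only: no extra participants, visits or data. The stated capability of the trial becomes more modest, and the independently justified difference has to be found and defended when the definitive trial is planned.

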### Qualitative phase

To ascertain participants’ views and experiences of the remodeled CEI, 12 participants from both stroke units will be purposefully selected for in-depth interview. The sample will include three participants who were randomized to the control group. It is likely that experiences of the CEI will be influenced by participants’ gender, age, disability and the artist involved in intervention delivery. Therefore, we will purposively select male and female participants of different age groups and with different levels of disability. The interviews will explore experiences, beliefs and attitudes about the CEI, the values and meaning placed on engagement in the CEI and its perceived effects. The interviews will also seek to examine how participation in the CEI is translated into meaningful benefits. Finally, the ways in which the CEI was perceived in relation to other forms of rehabilitation will be explored along with the experience and acceptability of participation in a trial.

The consent process at study recruitment will invite participants to agree to be contacted at the end of the study for participation in an interview. Participant interviews will be carried out after the three-month follow-up assessment. Our pre-study qualitative work showed that a total of approximately 12 participants is sufficient to reach the point at which no new findings emerge [58]. Focus groups with staff on each unit and interviews with artists will be conducted after the intervention phase of the study is complete. Written informed consent will be obtained at that time. One focus group of approximately six staff who have been involved in supporting the trial will be conducted at each site and will include staff from a range of disciplines, including support staff.

With participants in the intervention group we will explore their reasons for and experiences of taking part in the trial and their perceptions of acceptability and perceived usefulness of the CEI. We will examine the perceived value and meanings they ascribe to participation in the CEI and the impact of their preference for art on trial participation and perceptions of the CEI. Finally, we will ask about their perceptions of art participation as part of rehabilitation and any impact the CEI participation has had on their life after rehabilitation.

With the control group we will explore their reasons for and experiences of taking part in the trial and the impact that preference for art had on their participation. We will also examine their perceptions of art as part of rehabilitation and any changes that they made to their behavior as a result of trial participation. Finally we will explore any impact that the control intervention had on their life after rehabilitation.

We will ask staff and artists about their experiences and their perceptions of acceptability of all elements of the trial. We will also explore any perceived impact the trial had on usual practice and examine how they view the role of the CEI as part of rehabilitation. Finally, we will examine their views about the perceived effects the intervention had on participants.

### Data management and analysis

To ensure anonymity of data, interview transcripts will be given a study code and identifiable data within transcripts will be changed to ensure anonymity. Nvivo 9 (QSR International, Daresbury, United Kingdom) will be used to manage the data. We will use the Framework Approach, which was developed by the National Centre for Social Research in the UK, and is widely used for analysis of policy and health related qualitative data [59]. Framework provides a systematic approach to classification and organization of data in terms of emerging themes and patterns. Analysis will be iterative. New issues identified from interviews will be iteratively included in subsequent interviews for further exploration. A coding frame will be developed from data within the transcripts and from key psychological concepts identified from the pre-study interviews. We will apply the coding framework to all transcripts and emerging categories and themes will be added to the framework as they emerge. After all transcripts have been coded, the coding frame will be refined by review of each category, and by seeking association between themes and grouping them under more comprehensive, higher order themes.

To ensure trustworthiness of the analytical process, two researchers will check data coding for accuracy and we will examine our interpretations by constantly searching for alternative explanations. We will also discuss emerging themes and patterns and concepts with the wider research team. We will use findings from the qualitative research alongside findings from the feasibility trial to design the full RCT.

### Study timeline

The total study duration is 24 months. The study start date was the 1 March 2013. The pre-trial qualitative work and definition of trial outcome measures was conducted between 1 March 2013 and 31 July 2013. Trial recruitment is between 29 July 2013 and 30 July 2014. Baseline data is being collected from 9 July 2013 until all patients are recruited. Intervention delivery is between 29 July 2013 and 31 July 2014. End of intervention outcome assessment is between 22 August 2013 and 31 July 2014, with follow-up outcome assessment between November 2013 and November 2014. Qualitative interviews of participants who have completed the intervention are between January 2014 and November 2014. Trial data analysis will start in November 2014 and the planned study end date is the 28th February 2015.

### Dissemination plans

Two former stroke patient participants are members of our expert steering group as equal contributors and will advise on dissemination strategy. As per ethics committee requirements, we will write to all participants informing them of the study findings. To disseminate information to practitioners, we will also present our findings to acute stroke units, appropriate rehabilitation centers and relevant arts in health organizations across Scotland. We will also present findings through lectures at therapy meetings and local and national special interest groups, such as the Stroke Association, Chest, Heart and Stroke Scotland and others. To disseminate findings to academic audiences, we plan to publish our findings in high-impact peer-reviewed medical, therapy, and arts in health journals. We will also present findings at national and international therapy, medical and arts in health conferences and report findings in the clinicaltrials.gov database.

## Discussion

There is growing interest in the role that participation in the arts can provide in healthcare settings. Evidence is also emerging that art participation can augment rehabilitation, help to address the psychosocial effects of stroke and prepare survivors for fulfilling lives after rehabilitation. Providing such an intervention in rehabilitation settings is potentially costly, therefore its effects should be evaluated in the same way as other healthcare interventions, using robust scientific methods. Furthermore, assuming that art participation is a valuable adjunct to rehabilitation, it is vital that we seek to understand how it works and the outcomes that it influences. In line with other rehabilitation interventions, such understanding will enable us to refine the intervention to target it at those most likely to derive its known benefits.

However, the creative and apparently subjective nature of art participation means that designing a trial to test its effects is challenging. Our preparatory qualitative work based on the Medical Research Council’s (MRC) Framework for complex intervention design has enabled us to define the stages of the CEI and to provide a framework that is replicable, based on the core elements of an existing program. Our study endorses the importance of qualitative preparatory work as a precursor to trial design for complex interventions. This work enabled us to define the ways in which the intervention appears to work and the outcomes it appears to influence. The feasibility trial will enable us to undertake preliminary testing of these hypotheses and to determine feasibility issues associated with undertaking a trial of this nature in rehabilitation settings. Furthermore, qualitative interviews with participants at the end of the trial will enable us to confirm or disconfirm the effects of the CEI and our selection of outcome measures, and to refine the design of a full-scale definitive RCT.

To our knowledge, this is the first study aimed at examining the feasibility of using trial methods to evaluate the effectiveness of an art intervention for stroke survivors in rehabilitation. We hypothesize that participation in a CEI will improve the psychosocial outcomes for stroke survivors during and after rehabilitation. If shown to provide effect sizes, indicative of meaningful effects this intervention has the potential to address aspects of stroke recovery previously not addressed in rehabilitation, and will provide convincing evidence of benefits to healthcare providers and funders.

## Trial status

Recruitment started in July 2014 and finished in August 2014.

## Abbreviations

CEI: Creative engagement intervention
RCT: Randomized controlled trial
TCEI: Tayside creative engagement intervention
TCTU: Tayside Clinical Trials Centre
MOCA: The Montreal Cognitive Assessment
NIHSS: The National Institutes of Health Stroke Scale
PA: Positive Affect
NA: Negative Affect, NRC, Medical Research Council.
